## **Analysis of secondary endpoints**

The following analyses will be conducted with the FAS.

1. Proportional change in geometric mean of UACR at 12 and 24 weeks after the protocol treatment initiation as compared to that at baseline (important secondary endpoint):
2. Descriptive statistics calculations will be conducted, and histograms will be plotted for UACR and its participant-level proportional change by treatment group and study visit. Inferential statistics calculations will be conducted for the geometric mean of population-level UACR and its proportional change by treatment group and study visit.
3. Change in logarithmic UACR values at 12 and 24 weeks will be analyzed using a mixed-effects model (MMRM) with the logarithmic baseline value as a covariate, allocation, study visit and their interactions as fixed effects, and the patient as a random effect. The restricted maximum likelihood (REML) method will be used for the analysis with a compound symmetry structure specified as the covariance structure. The Kenward–Roger method will be used to calculate the degrees of freedom. To assess treatment effects, the between-group ratio of the proportional change in UACR geometric mean using the least squares mean at 12 weeks and the between-group ratio of the proportional change in UACR geometric mean using the least squares mean at 24 weeks will be estimated using the placebo group as the reference. At each time point, the output will be *P* value for testing the null hypothesis that the between-group ratio is 1.
4. Proportional change in geometric mean of blood biomarkers (pentosidine) and urinary biomarkers (type IV collagen, α1-MG, β2-MG, NGAL, NAG, L-FABP creatinine ratio) at 24 weeks after the protocol treatment initiation as compared to that baseline:
5. Descriptive statistics will be calculated, and histograms will be plotted for each item and its participant-level proportional change by treatment group and study visit. Inferential statistics calculations will be conducted for the population-level geometric mean and its proportional change by treatment group and study visit.
6. The logarithmic values of each item at 24 weeks will be analyzed using a linear regression model with the logarithmic values of baseline values as covariates and allocation as fixed effects. To assess treatment effect, the between-group ratio of the proportional change of the geometric mean using the least squares mean at 24 weeks will be estimated using the placebo group as a reference. The output will be *P* value of the test for the null hypothesis that the between-group ratio is 1.

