## Randomization procedure

Study participants will be randomly assigned using a central registration system. After confirming their eligibility, the principal investigators and co-investigators will promptly access the study’s website (EDC) and enter the required registration information. The information will be immediately verified on the EDC site, and if eligible, a patient identification number will be assigned. Then, dynamic allocation will be performed on the EDC.

Dynamic allocation to the finerenone and placebo groups will be performed using the minimization method in a 1:1 ratio with the following allocation stratification factors:

[Allocation factor]

Age at time of consent (< 70 years / ≥ 70 years)

Sex (female/male)

eGFR (< 60 mL/min/1.73 m^2^ / ≥ 60 mL/min/1.73 m^2^)*

Use of SGLT2 inhibitors at the time of consent (yes/no)

*Data obtained after obtaining consent will be prioritized; however, if such data cannot be obtained, data obtained within three months prior to obtaining consent may be used.

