　Next, in a subanalysis of the EMPA-TROPISM trial assessing patients with HFrEF (2), after six months of administration of the SGLT2 inhibitor empagliflozin, the change in vascular stiffness assessed by aortic pulse wave velocity was –0.58 cm/s (–0.36 SD) in the empagliflozin group and +0.60 cm/s (+0.60 SD) in the placebo group, demonstrating a significant improvement with empagliflozin (estimated effect size is approximately –0.36 SD–0.60 SD = –0.96 SD), and at the same time, proteomic analysis revealed a reduction in some inflammatory biomarkers. Moreover, in the PROTECT trial (jRCT1071220089) assessing patients with type 2 diabetes, although not limited to patients with CKD, the average CAVI value was approximately 9 with an SD of approximately 1.5 (unpublished data). Using these values, –0.6SD approximately yields a CAVI of –1; thus, in this study, the CAVI value of approximately 9 is expected to lower by approximately 1. In studies focusing on patients with diabetes and the general population (3,4), the CAVI value increased by 0.5 with approximately 10 years of aging; thus, lowering the CAVI by 1 point is equivalent to delaying the progression of arterial stiffness by approximately 20 years, and is considered to be clinically significant.

　Although no studies have directly compared the clinical effects of finerenone and empagliflozin, based on previous studies, if we assume that finerenone will improve vascular stiffness similar to that by empagliflozin as observed in the EMPA-TROPISM trial, we conservatively estimated that the CAVI in SD units from baseline to 24 weeks after treatment initiation would be reduced by > –0.6 (63% of the effect detected in the EMPA-TROPISM trial, calculated as –0.96 × 0.63 = –0.6) in the finerenone group compared to that in the placebo group, and set the significance level at 5% on both sides, power at 80%, and dropout rate at 10%. Thus, the minimum number of cases required to detect a significant difference between the two groups was set at 100 (50 in each group).

References:

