## **Analysis of other endpoints**

The following analyses will be performed with the FAS.

1. Changes from baseline in vital signs (weight, BMI, eEV, blood pressure, pulse pressure, and pulse rate in the clinic, and blood pressure, pulse pressure, and pulse rate at home) at 4, 12, and 24 weeks after the protocol treatment initiation:
2. Descriptive statistics calculations will be conducted, and histograms will be plotted for each item and its participant-level change by treatment group and study visit. Inferential statistics calculations will be conducted for the population-level mean and its change by treatment group and study visit.
3. For each item at each time point, analysis will be performed using MMRM with the baseline values as covariates, allocation, study visit and their interactions as fixed effects, and the patient as a random effect. The REML method will be used for the analysis with compound symmetry structure specified as the covariance structure. The Kenward–Roger method will be used to calculate the degrees of freedom. To assess the treatment effect at each time point, the between-group difference in the change in the mean value using the least squares mean will be estimated using the placebo group as a reference. At each time point, the output will be the *P* value for testing the null hypothesis that the between-group ratio is 0.
4. Changes from baseline in blood test indices (serum creatinine, eGFR, serum cystatin C*, serum potassium, HbA1c*, plasma (or serum) aldosterone concentration**, plasma (or serum) renin activity or concentration**) at 4, 12, and 24 weeks after the protocol treatment initiation (*evaluated only at baseline, and 12, and 24 weeks; **evaluated only at baseline and 24 weeks):
5. Descriptive statistics calculations will be conducted, and histograms will be plotted for each item and its participant-level change by treatment group and study visit. Inferential statistics calculations will be conducted for the population-level mean and its change by treatment group and study visit. If the distribution of values deviates significantly from normal distribution, the proportional change will be described with estimation of the geometric mean and its proportional change as appropriate.

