## **Safety endpoints**

The following analyses will be performed with the SS. Reported adverse events will be assigned a low-level term (LLT) code using the Medical Dictionary for Regulatory Affairs, Japanese (MedDRA/J). The version of MedDRA/J used for the analysis will be the latest version at the time of database fixation.

1. Serum potassium levels (blood test parameter)
2. Descriptive statistics calculations will be conducted, and histograms will be plotted for serum potassium levels and its participant-level change by treatment group and study visit. Inferential statistics calculations will be conducted for the population-level mean and its change by treatment group and study visit. If the distribution of values deviates significantly from normal distribution, the proportional change will be described with the geometric mean and its proportional change as appropriate.
3. For serum potassium levels at each time point, analysis will be performed using MMRM with the baseline values as covariates, allocation, study visit and their interactions as fixed effects, and the patient as a random effect. The REML method will be used for the analysis with compound symmetry structure set as the covariance structure. The Kenward–Roger method will be used to calculate the degrees of freedom. To assess the treatment effect at each time point, the between-group difference in the change in the mean value using the least squares mean will be estimated using the placebo group as the reference. At each time point, the output will be the *P* value for testing the null hypothesis that the between-group ratio is 0.
4. The frequency of serum potassium levels exceeding 5.5 and 6.0 mEq/L, and falling below 3.5 mEq/L will be calculated for baseline, 4, 12, and 24 weeks after the protocol treatment initiation.
5. At 4, 12, or 24 weeks after the protocol treatment initiation, frequency of events with serum potassium exceeding 5.5 and 6.0 mEq/L, or falling below 3.5 mEq/L will be tabulated. The denominator for the tabulation will be the number of SS cases with serum potassium data after the protocol treatment initiation.
6. Hyperkalemia (adverse event)

The frequency of hyperkalemia reported as an adverse event will be tabulated. The denominator for the tabulation will be the SS.

1. Adverse events and side effects

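### The UACR repeated-measures model fixes compound symmetry, which forces equal variance at weeks 12 and 24 and miscalibrates both intervals if the true variances differ

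*Combined protocol and SAP*

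**What the plan says.** The SAP (Analysis of secondary endpoints, UACR) analyses change in log-UACR at weeks 12 and 24 with an MMRM. The terms are log baseline, allocation, visit and their interactions, with the patient as a random effect. On the covariance it says: "The restricted maximum likelihood (REML) method will be used for the analysis with a compound symmetry structure specified as the covariance structure". Degrees of freedom follow Kenward–Roger. A between-group ratio and a P value are produced separately for each of the two visits.

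The specification recurs elsewhere in the SAP:

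- Analysis of other endpoints, vital signs (weeks 4, 12 and 24): "The REML method will be used for the analysis with compound symmetry structure specified as the covariance structure".
- The same section, for blood tests marked with one asterisk (cystatin C and HbA1c, weeks 12 and 24).
- Safety endpoints, serum potassium (weeks 4, 12 and 24): "The REML method will be used for the analysis with compound symmetry structure set as the covariance structure".

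The protocol (Efficacy analysis) names an MMRM but no covariance structure, so the restriction enters only through the SAP. Neither document gives a heterogeneous or unstructured alternative, a robust variance, or a rule for checking the structure.

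**The concern.** Compound symmetry has one variance, shared by all visits, and one correlation, shared by all pairs of visits. UACR has only two post-baseline visits and so only one pair. The common correlation therefore restricts nothing there; the equal-variance part does. The vital signs and serum potassium have three visits, and for them both parts bind.

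Each UACR visit is tested on its own, without multiplicity adjustment, so each visit's standard error has to be right by itself. A pooled variance is right for both visits only when the two variances are equal. Otherwise the more variable visit gets a standard error that is too small and the other gets one that is too large. Kenward–Roger corrects for having estimated the covariance parameters in a small sample, taking the assumed structure as true. It does not protect against a wrong structure.

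At stake are the coverage and type I error of the visit-specific UACR results, and of the other endpoints modelled this way.

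**Working it through.** **The plan's own figure.** The documents give no calculation for UACR; the only one is for the primary endpoint. Its inputs are a 0.6 SD difference and "set the significance level at 5% on both sides, power at 80%, and dropout rate at 10" per cent. The normal approximation gives 2 × (1.96 + 0.8416)² / 0.6² = 43.6, so 44 per arm; 44 / 0.9 = 48.9, so 49 per arm and 98 in total. The t-based version gives 45 per arm, and 45 / 0.9 = 50, which is the stated 100. The plan's number is reproduced, and 50 per arm is used in the simulation below.

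**Inputs for the check.** From the SAP: two visits, compound symmetry, REML, two-sided 5%. Assumed, because the documents do not give it: r, the SD of log-UACR change at week 24 divided by that at week 12, varied in both directions around 1.

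**Formula.** With balanced data, compound symmetry estimates the mean of the two visit variances. The ratio of model-based to true standard error is then

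- week 24: √[(1 + 1/r²) / 2]
- week 12: √[(1 + r²) / 2]

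and the coverage of a nominal 95% interval is 2Φ(1.96 × ratio) − 1.

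Example, r = 1.25. Week 24: (1 + 0.64) / 2 = 0.82, square root 0.906, coverage 2Φ(1.775) − 1 = 92.4%. Week 12: (1 + 1.5625) / 2 = 1.281, square root 1.132, coverage 97.3%.

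| r (assumed) | SE ratio, week 24 | Coverage, week 24 | SE ratio, week 12 | Coverage, week 12 |
|---|---|---|---|---|
| 0.8 | 1.132 | 97.3% | 0.906 | 92.4% |
| 1.0 | 1.000 | 95.0% | 1.000 | 95.0% |
| 1.1 | 0.956 | 93.9% | 1.051 | 96.1% |
| 1.25 | 0.906 | 92.4% | 1.132 | 97.3% |
| 1.5 | 0.850 | 90.4% | 1.275 | 98.8% |

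**Simulation.** Further assumptions: 50 per arm, SD 0.6 at week 12, correlation 0.6, 10% missing at week 24. There were 4,000 runs per scenario, fitted by REML with Satterthwaite-type degrees of freedom standing in for Kenward–Roger.

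| r | Week-24 coverage, compound symmetry | Week-24 coverage, unstructured |
|---|---|---|
| 1.0 | 95.0% | 95.2% |
| 1.25 | 92.4% | 95.3% |
| 1.5 | 90.1% | 94.8% |

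At r = 1 the mean standard error is 0.124 under both structures, so the freer structure costs nothing visible when compound symmetry is true. At r = 1.5 it is 0.157 under compound symmetry and 0.186 unstructured.

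**Baseline slope.** The model has one baseline slope for both visits. With a true slope difference of 0.15 between visits and r = 1, simulated week-24 coverage under the planned model is still 95.0%.

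**Three visits, for illustration.** With assumed SDs 0.7, 0.85 and 1.0, the mean variance is (0.49 + 0.7225 + 1) / 3 = 0.7375, with root 0.859. The standard error ratio is 0.859 at week 24 (true alpha 9.2%) and 0.859 / 0.7 = 1.227 at week 4 (true alpha 1.6%).

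**Parameter count.** Compound symmetry has 2 parameters. Unstructured has 3 for two visits and 6 for three, so the extra is 1 and 4.

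**The case against.** The strongest reply is that the harm is conditional. No UACR SD by visit appears in the documents. At r = 1 there is no error, at 1.1 it is about one point of coverage, and below 1 the week-24 interval is conservative. The SAP bases its efficacy conclusion on CAVI, which is a single-visit regression and is untouched. It also plans descriptive statistics, including SDs, by group and visit, so unequal variances would be seen. All of this stands and limits the weight of the point. However, no rule says what to do if unequal variances are seen, and the restriction buys nothing at this sample size.

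Some stronger readings are tempting and are not supported:

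- *The week-24 UACR interval is wrong.* That would need visit-specific variances the documents do not contain.
- *Supplementary Table S2 shows the fault.* Its interval widths for the group difference are nearly constant over weeks 4, 12 and 24: systolic pressure 11.9, 12.0 and 12.0; eGFR 5.5, 5.6 and 5.6. An imposed common variance produces this, but so do truly equal variances. The table contains no UACR, and its footnotes do not name the covariance structure.
- *The single baseline slope adds to the problem.* It does not force equal variances, and it cost no coverage in the simulation.
- *The model cannot be identified.* A patient random intercept with independent residuals already implies compound symmetry, so the SAP may be describing one model twice, which is harmless. Only fitting both would leave two parameters that cannot be separated.
- *eGFR is covered too.* Read literally, the blood-test MMRM text applies to asterisked items, and eGFR carries no asterisk.

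**Conclusion.** The point holds in conditional form. The SAP fixes equal variance across separately tested visits without justification, check or alternative. If the week-24 SD of log-UACR change is 10% to 50% above the week-12 SD, week-24 coverage falls to between 93.9% and 90.4%, a true alpha of 6.1% to 9.6%. If it is 20% below, week 12 is the affected visit, at 92.4%. These SD ratios are assumptions, and the formula assumes balanced data; the simulation with 10% missing at week 24 agrees for r from 1 to 1.5. This is a worthwhile, low-cost improvement to the secondary and other analyses. It does not bear on the primary CAVI conclusion.

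**What to change.** For every MMRM in the SAP, specify an unstructured within-patient covariance, keep REML and Kenward–Roger, and drop the separate patient random effect. State a fallback order for non-convergence: heterogeneous Toeplitz, then heterogeneous compound symmetry. A baseline-by-visit term may be added but is optional. State also which model, if any, applies to the blood tests without an asterisk that are measured at three visits.

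The cost is SAP wording plus one variance parameter for UACR and four for each three-visit endpoint, which about 100 patients can support. Because the file already contains results, the unstructured fit for this trial should be reported as a labelled sensitivity analysis beside the pre-specified one, together with the SD of log-UACR change at each visit. Those SDs would show directly whether the concern has any practical size.

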## **Analysis of other endpoints**

The following analyses will be performed with the FAS.

1. Changes from baseline in vital signs (weight, BMI, eEV, blood pressure, pulse pressure, and pulse rate in the clinic, and blood pressure, pulse pressure, and pulse rate at home) at 4, 12, and 24 weeks after the protocol treatment initiation:
2. Descriptive statistics calculations will be conducted, and histograms will be plotted for each item and its participant-level change by treatment group and study visit. Inferential statistics calculations will be conducted for the population-level mean and its change by treatment group and study visit.
3. For each item at each time point, analysis will be performed using MMRM with the baseline values as covariates, allocation, study visit and their interactions as fixed effects, and the patient as a random effect. The REML method will be used for the analysis with compound symmetry structure specified as the covariance structure. The Kenward–Roger method will be used to calculate the degrees of freedom. To assess the treatment effect at each time point, the between-group difference in the change in the mean value using the least squares mean will be estimated using the placebo group as a reference. At each time point, the output will be the *P* value for testing the null hypothesis that the between-group ratio is 0.
4. Changes from baseline in blood test indices (serum creatinine, eGFR, serum cystatin C*, serum potassium, HbA1c*, plasma (or serum) aldosterone concentration**, plasma (or serum) renin activity or concentration**) at 4, 12, and 24 weeks after the protocol treatment initiation (*evaluated only at baseline, and 12, and 24 weeks; **evaluated only at baseline and 24 weeks):
5. Descriptive statistics calculations will be conducted, and histograms will be plotted for each item and its participant-level change by treatment group and study visit. Inferential statistics calculations will be conducted for the population-level mean and its change by treatment group and study visit. If the distribution of values deviates significantly from normal distribution, the proportional change will be described with estimation of the geometric mean and its proportional change as appropriate.
6. For each item marked with an "*," at each time point, analysis is performed using a MMRM with the baseline values as covariates, allocation, study visit and their interactions as fixed effects, and the patient as a random effect. The REML method will be used for the analysis with a compound symmetry structure specified as the covariance structure. The Kenward–Roger method will be used to calculate the degrees of freedom. To assess the treatment effect at each time point, the between-group difference in the change in the mean value using the least squares mean will be estimated using the placebo group as a reference. At each time point, the output will be the *P* value for testing the null hypothesis that the between-group ratio is 0.

For items marked with "**," analysis will performed using a linear regression model with baseline values as covariates and allocation as fixed effects for each item at 24 weeks. To assess the treatment effect, the between-group difference in the change using the least squares mean at 24 weeks will be estimated using the placebo group as a reference. The output will be *P* value for testing the null hypothesis that the between-group difference in change is 0.

In any analysis, if the distribution of values significantly deviates from a normal distribution, logarithmic values will be used for analysis as appropriate.

1. Changes from baseline in AI and % mean arterial pressure at 24 weeks after the protocol treatment initiation:
2. Descriptive statistics calculations will be conducted, and histograms will be plotted for each item and its participant-level change by treatment group and study visit. Inferential statistics calculations will be conducted for the population-level mean and its change by treatment group and study visit. If the distribution of values deviates significantly from normal distribution, the proportional change will be described with estimation of the geometric mean and its proportional change as appropriate.
3. Analysis will be performed using a linear regression model with baseline values as covariates and allocation as fixed effects for each item at 24 weeks. To assess the treatment effect, the between-group difference in the change using the least squares mean at 24 weeks will be estimated using placebo group as a reference. The output will be the *P* value for testing the null hypothesis that the between-group difference in change is 0. If the distribution of values significantly deviates from a normal distribution, logarithmic values will be used for analysis as appropriate.
4. Changes from baseline in cardiac function indices (LVEF, septal e', lateral e', E, E/e'*, LVMI, LAD, LAVI) assessed by echocardiography 24 weeks after the protocol treatment initiation:
5. Descriptive statistics calculations will be conducted, and histograms will be plotted for each item and its participant-level change by treatment group and study visit. Inferential statistics calculations will be conducted for the population-level mean and its change by treatment group and study visit. If the distribution of values deviates significantly from normal distribution, the proportional change described with estimation of the geometric mean and its proportional change as appropriate.
6. Analysis will be performed using a linear regression model with baseline values as covariates and allocation as fixed effects for each item at 24 weeks. To assess the treatment effect, the between-group difference in the change using the least squares mean at 24 weeks will be estimated using the placebo group as a reference. The output will be the *P* value for testing the null hypothesis that the between-group difference in change is 0. If the distribution of values significantly deviates from a normal distribution, the logarithmic values will be used for analysis as appropriate.
7. Changes in abundance of up to 181 proteins comprehensively analyzed by proteomic analysis (Olink Target 96 CVD III analysis, Olink Target 96 Inflammation analysis) at 24 weeks after the protocol treatment initiation as compared to that at baseline (exploratory endpoint):
8. Descriptive statistics calculations will be conducted for each item and its participant-level change by treatment group and study visit. If the distribution of values deviates significantly from normal distribution, the proportional change will be described as appropriate.
9. Comprehensive comparisons between groups will be performed for each variable using *t*-tests. The Benjamini–Hochberg method will be used to control the false discovery rate at < 5% under multiple comparisons.

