The change from baseline in each outcome at 24 weeks after the protocol treatment initiation will be analyzed using a linear regression model with the treatment group as a fixed effect factor and the baseline value as a covariate. Moreover, the mean values of both treatment groups at 24 weeks and their 95% confidence intervals, as well as the treatment effect estimated by the difference in the mean values between the treatment groups and their 95% confidence intervals will be calculated. A test will be performed against the null hypothesis such that the difference in treatment effect is 0. If the distribution of values deviates significantly from a normal distribution, appropriate scale conversion will be performed.

1. Changes in abundance of up to 181 proteins comprehensively analyzed by proteomic analysis (Target 96 panel) at 24 weeks after protocol treatment initiation as compared to that at baseline (exploratory endpoint):

Comprehensive comparisons between groups will be performed for each evaluation item using *t*-tests. The Benjamini–Hochberg method will be used to control the false discovery rate to 5% under multiple comparisons.

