## **Analysis of the primary endpoint**

The following analysis will be performed on the FAS as the primary analysis. Furthermore, an analysis will be conducted using the PPS to confirm the robustness of the results.

1. Descriptive statistics calculations will be conducted, and histograms will be plotted to assess CAVI and its participant-level change and proportional change by treatment group and study visit. Inferential statistics calculations will be used to estimate CAVI mean and change, and geometric mean and proportional change at population-level by treatment group and study visit.
2. As the primary analysis for the primary endpoint, change in CAVI at 24 weeks will be analyzed using a linear regression model with baseline values as covariates and allocation as fixed effects. To assess treatment effect, the between-group difference in CAVI change using the least squares mean at 24 weeks will be estimated using the placebo group as a reference. The output will be the *P* value of the test for the null hypothesis that the between-group difference in change is 0. Moreover, the presence or absence of a treatment effect will be determined using the criteria of a two-sided *P* value of < 0.05.
3. As a supplementary analysis for the primary endpoint, change in logarithmic CAVI at 24 weeks will be analyzed using a linear regression model with logarithmic baseline values as covariates and allocation as fixed effects. To assess treatment effect, the between-group ratio of the proportional change in CAVI geometric mean using the least squares mean at 24 weeks will be estimated using the placebo group as a reference. The output will be the *P* value of the test for the null hypothesis that the between-group ratio is 1.

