**Supplementary Table S3. Effect on circulating proteins from Cardiovascular III and Inflammation panels**

| **Protein** | **Panel** | **Major function** | **Effect estimate (finerenone minus placebo)*** | **Nominal *P* value** | **BH *P* value** |
| --- | --- | --- | --- | --- | --- |
| CST5 | Inflammation | Inhibition of cysteine proteinases | 0.188569 | 0.000774 | 0.142379 |
| GDNF | Inflammation | Enhancement of survival and morphological differentiation of dopaminergic neurons | 0.194652 | 0.006729 | 0.417406 |
| OPN | Cardiovascular III | Cell-matrix interaction; Inflammatory response | −0.245702 | 0.006806 | 0.417406 |
| CD244 | Inflammation | Inflammation: Immune response | 0.117030 | 0.019069 | 0.559225 |
| CHI3L1 | Cardiovascular III | Angiogenesis; Inflammatory response | −0.323429 | 0.022454 | 0.559225 |
| t-PA | Cardiovascular III | Antithrombotic action | −0.227057 | 0.023265 | 0.559225 |
| MMP-3 | Cardiovascular III | Degradation of cartilage and connective tissue | −0.206002 | 0.024168 | 0.559225 |
| ST2 | Cardiovascular III | Inflammation; Cell proliferation; Fibrosis | −0.169734 | 0.024463 | 0.559225 |
| CTSD | Cardiovascular III | Angiogenesis; Inflammatory response | −0.131026 | 0.028905 | 0.559225 |
| TNFRSF9 | Inflammation | Cell survival and differentiation; Immunity | 0.142584 | 0.030393 | 0.559225 |
| CD6 | Inflammation | Cell adhesion; T-cell activation | 0.124113 | 0.034674 | 0.579999 |

Six proteins (OPN, CHI3L1, t-PA, MMP-3, ST2, and CTSD) were downregulated (blue cells) with finerenone therapy compared with placebo, and five proteins (CST5, GDNF, CD244, TNFRSF9, and CD6) were upregulated (red cells).

* Based on log2 fold change from baseline in normalized protein expression at week 24.

BH, Benjamini-Hochberg method; CHI3LI, chitinase-3 like-protein-1; CST5, cystatin D; CTSD, cathepsin D; GDNF, glial cell line-derived neurotrophic factor; MMP-3, matrix metalloproteinase-3; OPN, osteopontin; ST2, suppression of tumorigenesis-2; TNFRSF9, tumor necrosis factor receptor superfamily member 9; t-PA, tissue-type plasminogen activator.

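### The exploratory proteomic endpoint is compared with unadjusted t-tests, although the protocol adjusts every other continuous efficacy endpoint for baseline; the test is valid but gives up precision.

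*Combined protocol and SAP*

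**What the plan says.** The endpoint is listed last among the other endpoints and labelled exploratory: "Changes in abundance of up to 181 proteins comprehensively analyzed by proteomic analysis", at week 24 compared with baseline. For the test, the SAP (Analysis of other endpoints) states "Comprehensive comparisons between groups will be performed for each variable using" *t*-tests, and that the Benjamini-Hochberg "method will be used to control the false discovery rate at < 5% under multiple comparisons". The protocol (Efficacy analysis, other endpoints) has the same rule: "Comprehensive comparisons between groups will be performed for each evaluation item using" *t*-tests. No covariate is named in either place.

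The test sentence does not itself say that change is the variable tested. That follows from the endpoint definition and from the footnote to Supplementary Table S3: "Based on log2 fold change from baseline in normalized protein expression at week 24". The log2 scale appears only in that footnote, not in the plan.

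The other endpoints are handled differently. For the primary endpoint, the SAP says "change in CAVI at 24 weeks will be analyzed using a linear regression model with baseline values as covariates and allocation as fixed effects". UACR is modelled "with the logarithmic baseline value as a covariate". Pentosidine and the urinary biomarkers, which like the proteins are measured only at baseline and week 24, are modelled with "logarithmic values of baseline values as covariates and allocation as fixed effects". The protocol also includes the baseline value in its models for vital signs, blood tests, augmentation index, % mean arterial pressure and echocardiography.

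**The concern.** A *t*-test on change fixes the coefficient of the baseline value at 1. A model with baseline as a covariate estimates that coefficient, and for a noisy biomarker it is usually below 1. The change score then carries baseline variation that the model would have removed. The baseline sample is already scheduled for this endpoint, so the information costs nothing to use.

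The loss matters more than usual here because false discovery control over about 181 tests demands small P values. At the first Benjamini-Hochberg step the threshold is 0.05/181 = 0.000276, where power is low and a modest change in variance moves it noticeably. At stake is the sensitivity of an exploratory screen, not the trial's efficacy conclusion.

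**Working it through.** **The plan's own figure.** The documents give no power calculation for proteomics, only the sample size for CAVI: 0.6 SD, two-sided 5%, 80% power, 10% dropout, 100 patients. The normal formula gives n per arm = 2(1.96 + 0.8416)²/0.6² = 43.6, so 44; the *t*-based calculation gives 45. Dividing by 0.9 gives 49 and 50 per arm, or 98 and 100 in total. The figure of 100 reproduces, and 45 per arm is the planned analysable number used below.

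**Variance.** Let s0 and s1 be the SDs at baseline and week 24, and rho their within-group correlation. Apart from a common factor for sample size:

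- *t*-test on change: s0² + s1² − 2·rho·s0·s1
- linear model with baseline: s1²(1 − rho²)
- difference between the two: (s0 − rho·s1)², which is never negative

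With s0 = s1 the ratio of the second to the first is (1 − rho²)/[2(1 − rho)] = (1 + rho)/2. The covariate costs one degree of freedom (87 instead of 88 at 45 per arm), which is negligible.

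**Size.** Assumptions, none given in the documents: rho as shown, and a true effect of 0.6 SD of change. The strictest-step columns use the noncentral *t* at alpha = 0.05/181. The average-power columns come from 600 simulated runs of Benjamini-Hochberg at 5% with 181 independent proteins, 18 of them truly affected.

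| rho | variance ratio | 45 per arm becomes worth | power at strictest step: *t*-test → adjusted | average power under BH: *t*-test → adjusted |
|---|---|---|---|---|
| 0.9 | 0.95 | 47.4 | 18.5% → 20.4% | 39.3% → 42.3% |
| 0.8 | 0.90 | 50.0 | 18.5% → 22.7% | 39.2% → 46.1% |
| 0.7 | 0.85 | 52.9 | 18.5% → 25.3% | 37.6% → 48.3% |
| 0.5 | 0.75 | 60.0 | 18.5% → 31.8% | 38.0% → 59.1% |

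The small differences among the *t*-test values in the last column are simulation noise.

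**Validity.** In these runs the false discovery rate was 3.9% to 5.2% for the *t*-test and 4.2% to 4.8% for the adjusted model. In a separate simulation with no treatment effect (45 per arm, 100,000 runs per correlation), the type I error at rho 0.5, 0.7 and 0.9 was 4.9%, 5.0% and 4.9% for the *t*-test, and 4.9%, 4.9% and 5.0% for the adjusted model.

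**Number of tests.** Where a Benjamini-Hochberg value is set by its own rank, the number of tests is that value × rank / nominal P. From Supplementary Table S3:

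- rank 1: 0.142379/0.000774 = 183.95
- rank 3: 0.417406 × 3/0.006806 = 183.99
- rank 11: 0.579999 × 11/0.034674 = 184.00

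So 184 tests were corrected for, against a planned maximum of 181.

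**The case against.** The best defence is that a valid, prespecified test with false discovery control is a reasonable exploratory screen. That stands: the *t*-test is not an error, and the SAP rests efficacy on the primary analysis of CAVI in the full analysis set. It is also true that the loss cannot be sized from the documents and is slight if correlations are near 0.9.

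Several stronger readings are tempting and are not supported:

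- *That chance baseline imbalance across so many proteins generates false leads.* For one protein with a visible imbalance, the change score is indeed biased conditionally on that imbalance. Under randomisation, though, the *t*-test's 5% error rate already includes such imbalances, and the simulations show no excess of false positives.
- *That adjustment would have produced a discovery.* The smallest nominal P is 0.000774 against a first step of 0.05/184 = 0.000272. With the estimate held fixed and about 90 degrees of freedom (assumed), *t* would have to rise from 3.480 to 3.790. That is a variance ratio of (3.480/3.790)² = 0.843, or rho of about 2 × 0.843 − 1 = 0.69 or lower. The estimate would also move on adjustment, so this shows sensitivity and predicts nothing.
- *That proteomics carries the trial's mechanistic conclusion.* The protocol presents it as exploratory and complementary to the primary and secondary endpoints.
- *That 181 is the count of distinct proteins, so 184 is wrong.* The documents say only up to 181 and do not explain either figure.

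One qualification concerns the comparison with other endpoints. It is exact in the protocol. The SAP's blood-test section gives models only for items marked with one or two asterisks, so serum creatinine and eGFR have no literal model there. The protocol's baseline-adjusted models cover them, and the SAP declares no changes from the research plan.

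**Conclusion.** The point holds as one of efficiency and consistency. The proteomic comparison departs, without a stated reason, from the baseline adjustment that the protocol uses for every other continuous efficacy endpoint. Under equal variances the avoidable variance is 5% to 25% for assumed correlations from 0.9 down to 0.5. At the strictest step, power for an assumed effect of 0.6 SD of change rises from 18.5% to between 20.4% and 31.8%. The direction does not depend on the equal-variance assumption, apart from the trivial cost of one degree of freedom; the size does depend on it and on the unknown correlations. Type I error, false discovery control and the primary conclusion are unaffected. The mismatch between 181 and 184 barely moves the first threshold (0.000276 against 0.000272) and is a matter of reconciliation.

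**What to change.** For each protein, fit a linear model of the week-24 level (or its change), on the log2 normalized expression scale, with treatment and the baseline level as terms. Apply Benjamini-Hochberg at 5% to the treatment P values. State the scale in the SAP, since at present only the results footnote gives it.

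Because the *t*-test results are already in the supplementary material, present the adjusted analysis as additional and label it as specified after the results were available. Keep the prespecified *t*-tests beside it, and show both sets of estimates and adjusted P values.

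State how many tests form the Benjamini-Hochberg family, and explain why Supplementary Table S3 implies 184 when the plan says at most 181.

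The cost is a line in the SAP, a changed model call, one degree of freedom per protein and a second results column. No new data are needed.
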